### Study schema and interim analysis

TROCAR has been designed with an internal pilot phase of 6 months’ duration (Fig. 1). During this time, we aim for 84 patients to be randomised. An interim analysis will be presented to the DMC after the internal pilot phase to confirm adequate recruitment and to monitor safety. A report will be compiled by the trial statistician, which will be presented to the DMC. The trial will continue to progress while the interim analysis is prepared. Participants from the internal pilot will contribute to the final analysis. In total, it is anticipated recruitment will take 12–18 months.

**Fig. 1 Fig1:**
[figure not shown]
Study designed with an internal pilot with progression to the ‘full trial’ dependent on achieving adequate recruitment in 6 months

### Progression criteria

The internal pilot analysis will present total participants recruited, monthly recruitment rates and available secondary outcome data. Criteria for trial progression are outlined in Table 2. If all criteria are green, the trial will continue without protocol modification; if one or more criteria are amber, adaptations may be proposed to address the shortfall; one or more red criteria will require discussion about whether ongoing participant recruitment is feasible.

**Table 2 Tab2:** Progression criteria stipulated at the interim analysis at 6 months

Criterion	Target	Green	Amber	Red
Participant recruitment	84	≥ 60	35–59	< 34
Randomisation rate (minimum number recruited per month)	14	≥ 9	5–8	< 5
Secondary outcome data available	80%	≥ 70%	50–70%	< 50%

In addition to recruitment analysis, the DMC will examine the unblinded frequency and severity of adverse events. If serious adverse events occur during the internal pilot that are assessed to be directly related to Duramesh and/or are disproportionately associated with Duramesh compared to conventional suture, then the DMC has the option to recommend trial termination. No specific number is declared, but judgement will be based on the severity of harm and its frequency relative to conventional suture.

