### Sample size

This study will be powered for detecting a difference in the primary outcome between groups. Previous prospective studies with similar follow-up duration record an incidence of trocar-site hernia in the region of 25% [7–9]. An absolute reduction in primary outcome of 15% is expected within the intervention group, down to an occurrence of 10%. The best available evidence comes from a systematic review of Duramesh implantation for laparotomy and ventral hernia repair with a median incisional hernia rate of 3.4% after 1 year [13]. An occurrence of 10% was selected as a conservative estimate of the effect size in the intervention group after 2 years. Therefore, using a significance level of 5% and power of 80%, it is calculated that 100 patients per group, 200 in total, are required. After factoring in a 20% rate of loss to follow-up, a total of 250 participants will be included in the trial.

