### Loss to follow-up

Our sample size calculations have factored in a 20% rate of loss to follow up, which is based on other studies in surgical populations requiring 2-year follow-up with imaging to detect incisional hernia [19, 20]. By consenting to participate, patients are consenting to the intervention, assessments, follow-up and data collection. Study participants are free to withdraw at any time.

Participants may be withdrawn from the trial by the research team if continued participation is no longer in their best interests. Reasons for discontinuing may include the following: intercurrent illness making data collection impossible, persistent non-compliance with protocol requirements hampering and/or biasing data collection, participant fulfils any of the intra-operative exclusion criteria, and participant loss to follow-up (e.g. moves abroad/not contactable).

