### Statistical methods

Results will be reported in accordance with the CONSORT guidelines for randomised controlled trials [21]. Analyses will be on an intention-to-treat (ITT) basis and will be conducted according to a pre-specified statistical analysis plan. The primary analyses will use data from all participants randomised who provided written informed consent, whose data is suitable (i.e. not missing). Any missing data will be reported, and data will be summarised as observed without imputation. Missing data values will be omitted from the primary analyses.

Continuous demographic variables such as age and BMI will be summated by the mean ± standard deviation if found to be normally distributed, and median with range or inter-quartile range otherwise. Categorical variables will be summarised by the number and percentage in each category.

To allow for differences in outcomes between participating surgeons, all analysis will be performed using generalised mixed (multilevel) models. Study group will be included as a fixed effect, with surgeon as a random effect. The primary outcome, the occurrence of trocar-site hernia over 2 years, will be analysed using a model assuming a binomial distribution with an identity link function. This will enable the percentage difference in outcome between groups to be calculated, which will be presented with a corresponding confidence interval. Secondary outcomes measured on a binary scale will be analysed using an equivalent approach to the primary outcome. Length of stay in hospital will be analysed using a linear mixed model. This outcome is expected to follow a positively skewed distribution and will thus be given a log transformation before analysis. All tests will be two-sided and a *p* value < 0.05 will be considered as statistically significant. Confidence intervals will be calculated at the 95% level.

A sensitivity analysis will be performed for the primary outcome. This will use multiple imputation for patients with missing outcome data. This will be performed using chained equations.

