### Trial status

Ethical approval was received on 10th April 2025 by Cambridge Central Research Ethics Committee, reference number 25/EE/0057. The study was registered in the public domain and given International Standard Randomised Controlled Trial Number (ISRCTN) 14473961. The first TSC and DMC meeting was held in May 2025 with study termination rules and minor amendments to the protocol authorised. The latest version of the protocol is version 2.2. Recruitment began in June 2025 and is anticipated to complete by December 2026.

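### Table 2's progression bands leave a gap at 34 recruits and an overlap at 70%, and the green recruitment floor is not tied to the planned recruitment period

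*Protocol article*

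**What the plan says.** The section on progression criteria scores three items at the end of the 6-month internal pilot. 

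- **Participants recruited:** target 84, green at 60 or more, amber 35–59, red below 34.
- **The row labelled** "Randomisation rate (minimum number recruited per month"**:** target 14, green at 9 or more, amber 5–8, red below 5.
- **Secondary outcome data available:** target 80%, green at 70% or more, amber 50–70%, red below 50%.

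The rule attached to the best result is "If all criteria are green, the trial will continue without protocol modification". One or more ambers allows adaptations to be proposed. One or more reds calls for a discussion of feasibility.

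Elsewhere, the section on study schema and interim analysis expects recruitment to take 12–18 months, and the trial status section states "Recruitment began in June 2025 and is anticipated to complete by December 2026". The total is 250. On attrition, the loss to follow-up section says "Our sample size calculations have factored in a 20% rate of loss to follow up", and bases that rate on studies with 2-year imaging.

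**The concern.** A progression table has to assign every possible result to exactly one band, and this one does not. Its green band should also mean that the trial is broadly on course, because green is the result that prompts no action. Here the lowest green recruitment count corresponds to a pace well below what the stated recruitment period needs. The green floor for data completeness likewise accepts more missing data at the pilot review than the plan allows over 2 years. What is at stake is an early prompt: a recruitment shortfall could pass the formal pilot check unremarked while it is still easy to correct.

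**Working it through.** **The plan's own figures first.** Inputs from the sample size section: "record an incidence of trocar-site hernia in the region of 25" per cent in controls; "An absolute reduction in primary outcome of 15% is expected within the intervention group, down to an occurrence of 10" per cent; and "using a significance level of 5% and power of 80%, it is calculated that 100 patients per group, 200 in total, are required". The statistical methods section adds "All tests will be two-sided".

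Pooled two-proportion formula, with mean proportion 0.175:

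n per arm = [1.960 × √(2 × 0.175 × 0.825) + 0.842 × √(0.25 × 0.75 + 0.10 × 0.90)]² / 0.15² = 99.5, rounded up to 100 (power 80.2%).

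Allowing for 20% loss: 200 / 0.8 = 250. The sample size reproduces and is not in question.

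**Target against timeline.** 84 / 6 = 14 a month, and 250 / 14 = 17.9 months. The target column therefore fits the plan, at its 18-month end.

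**Pace the plan needs.**

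| Recruitment period | Rate for 250 | Count at month 6 |
|---|---|---|
| 12 months | 20.8 a month | 125 |
| 18 months | 13.9 a month | 83–84 |
| 19 months (June 2025 to December 2026, both months included) | 13.2 a month | 79 |

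**Green floor against timeline.** 60 / 6 = 10 a month.

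- Time to 250 at that pace: 250 / 10 = 25 months.
- Recruited by month 18: 180; by month 19: 190.
- Rate needed after month 6 to finish by month 18: (250 − 60) / 12 = 15.8 a month, 58% above the pace just scored green. By month 19: 190 / 13 = 14.6 a month. Both exceed the target of 14.

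The floor of 9 a month does not lower this bound. 9 × 6 = 54, which is amber on the count, so 60 is the smallest count that can be all green.

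**Boundaries.** Of all whole-number counts, only 34 fails every test: it is not 60 or more, not within 35–59, and not below 34. A value of exactly 70% meets both the green and the amber definition.

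**Data floor against attrition.** The target of 80% equals 100% − 20%. The green floor of 70% accepts 30% missing.

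**Conditional power** (same formula; neither condition is stated in the protocol):

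- Recruitment stops at 180 with 20% loss: 144 evaluable, 72 per arm. z = [0.15 × √72 − 1.960 × √0.28875] / √0.2775 = 0.417, power 66.2%.
- All 250 recruited, but 30% missing on the primary outcome: 175 evaluable, 87.5 per arm, power 74.7%.

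**The case against.** The best defence is that green is a tolerance floor and the target column carries the plan: 14 a month gives 17.9 months, and 80% matches the 20% allowance. A slow start can be recovered. The surgeons perform about 750 laparoscopic operations a year, roughly 62 a month, although not all those patients will be eligible, and 15.8 a month is about a quarter of that. The 12–18 months and the December 2026 date are anticipations, and nothing in the article closes recruitment then. The steering and monitoring committees also meet every 6 months, so Table 2 is not the only safeguard.

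Much of this stands, and it rules out several stronger readings:

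- **That a trial unable to meet its plan is scored green.** At the green floor the trial is off pace, not beyond recovery.
- **That the bands themselves cost power.** Slow accrual costs time. A power loss needs an early stop, or 30% missing carried over to the primary outcome, and the article states neither.
- **That the data row contradicts the attrition assumption.** One figure concerns secondary outcomes at the pilot review, the other imaging at 2 years.
- **That the two recruitment rows contradict each other.** They can land in different bands, but the rule of one or more amber or red settles the outcome.
- **That the data row cannot be met because few participants have reached 90 days by month 6.** This presumes that all randomised participants form the denominator. The article names none, and a condensed article may leave that to the full protocol.

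The defence does not answer the gap at 34, the overlap at 70%, or the fact that a pace projecting to 25 months is scored as needing no change.

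**Conclusion.** The point holds in limited form. The two boundary faults are certain from the table itself, though each affects a single value. The green recruitment floor is out of step with the stated period: 25 months at a constant 10 a month, against 12–18, with 15.8 a month needed afterwards to recover. That projection assumes a constant rate; a pilot that starts slowly and accelerates would finish sooner. The expected cost is delay. The 66% power figure applies only if recruitment ended at 180 with 20% loss. The 70% data floor is looser than both its own target and the 2-year allowance. It deserves notice as a misalignment, since 30% missing at the pilot review would already exceed the whole 2-year allowance if those participants did not return.

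**What to change.** 1. **Close the bands.** Define red as 34 or fewer, or extend amber to 34–59. Define amber for data availability as 50% to below 70%.
2. **Tie the green recruitment floor to the timeline.** Either raise it towards the count that the 18-month plan needs by month 6, about 83–84, or keep 60 and restate the anticipated recruitment period as up to about 25 months at that floor. Some tolerance below target is legitimate; its consequence for the end date should be stated.
3. **Data row.** Acknowledge that the 70% floor is below the 80% implied by the loss allowance. Setting green equal to target in every row would be a preference and is not required.

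The cost is an edit to one table with committee agreement. With a higher floor, a trial slightly below target may score amber, which only allows adaptations to be proposed. Recruitment began in June 2025, so the 6-month review may already have taken place. If so, record the change as made after the counts were known, and do not re-score the pilot.

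### The progression bands in Table 2 do not fit together: 34 patients has no colour, 70% has two, and the total and monthly-rate rows share a target but not cut-points

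*Protocol article*

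**What the plan says.** Under Study schema and interim analysis, the protocol article states that "TROCAR has been designed with an internal pilot phase of 6 months’ duration" and, for that period, "we aim for 84 patients to be randomised". Table 2, under Progression criteria, then gives three rows:

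| Row | Target | Green | Amber | Red |
|---|---|---|---|---|
| 1. Participants recruited | 84 | ≥ 60 | 35–59 | < 34 |
| 2. Monthly rate | 14 | ≥ 9 | 5–8 | < 5 |
| 3. Secondary outcome data | 80% | ≥ 70% | 50–70% | < 50% |

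Row 2 is labelled "Randomisation rate (minimum number recruited per month". The rows are combined by a three-part rule. At the top level, the trial simply goes on when every row is green. At the middle level, the article says that "if one or more criteria are amber, adaptations may be proposed to address the shortfall". At the lowest level, its wording is that "one or more red criteria will require discussion about whether ongoing participant recruitment is feasible". In effect the worst row decides.

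**The concern.** A pre-specified progression rule should give one colour per row for every possible result. Table 2 does not. Two faults lie within single rows: a gap at 34 patients and an overlap at 70%. A third lies between the two recruitment rows, whose targets are one quantity on two scales while their cut-points are not.

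The row 2 label adds an ambiguity. It can mean the minimum acceptable average rate, or the count in the slowest month. The first makes row 2 nearly redundant. The second makes it a separate criterion that is sensitive to month-to-month chance.

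At stake is the clarity of the report that the Data Monitoring Committee (DMC) receives. Two people applying the table to the same pilot could report different colours.

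**Working it through.** **Inputs.** Pilot length of 6 months and target of 84 (Study schema and interim analysis); the bands and the combination rule (Progression criteria, Table 2).

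**The plan's own figure.** 14 per month × 6 months = 84. The two recruitment targets agree exactly.

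**Gaps and overlaps within rows.**
- Row 1, whole numbers: red covers 0–33, amber 35–59, green 60 and above. Only 34 is left without a colour.
- Row 3, whole percentages: only 70% meets two definitions (green ≥ 70%, amber 50–70%).

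**Rows 1 and 2, with row 2 read as a 6-month mean.** Row 2 cut-points as totals: 9 × 6 = 54 and 5 × 6 = 30. Row 1 cut-points as rates: 60/6 = 10.0 and 35/6 = 5.83.

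| Total | Mean per month | Row 1 | Row 2 |
|---|---|---|---|
| 0–29 | below 5 | red | red |
| 30–33 | 5.00–5.50 | red | amber |
| 34 | 5.67 | none | amber |
| 35–48 | 5.83–8.00 | amber | amber |
| 49–53 | 8.17–8.83 | amber | none |
| 54–59 | 9.00–9.83 | amber | green |
| 60 or more | 10.0 or more | green | green |

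With the worst row deciding, 30–33 is red overall, and both 49–53 and 54–59 are amber overall. Row 2 affects the outcome only at 34, where it supplies the one available colour.

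**Rows 1 and 2, with row 2 read as the lowest single month.** The rows now measure different things, and neither is always the stricter:
- Nine patients in every month gives 54 in total: green on row 2, amber on row 1.
- A total of 60 or more with one month at 8 or below: green on row 1, amber or red on row 2.

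To size the second case a model is needed, because the article gives no month-to-month variability. Assume independent Poisson months at a constant rate.
- At the full target of 14 per month: P(8 or fewer in a month) = 0.062, so P(at least one of six months below 9) = 1 − (1 − 0.062)^6 = 0.32.
- The pilot total is then Poisson with mean 84, and P(60 or more) = 0.997.
- Among simulated pilots reaching 60 or more, the share not green on row 2 is 61% at a true rate of 12 per month and 83% at 10 per month. These two rates are illustrative and do not come from the article.

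**The case against.** The best defence is that the combination rule already absorbs most of this. Total recruitment and monthly rate are listed as separate items for the pilot report, separate criteria may take different colours, and the any-amber, any-red rule exists to combine them. That stands: 30–33 and 54–59 do get an overall colour. Even 34 does not leave the pilot unclassified, because row 2 is amber on the mean reading and, since the lowest of six months cannot then exceed 5, amber or red on the other. What the rule cannot settle is whether 34 was meant to be red or amber on row 1, or which colour 70% takes.

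A reader might infer that row 2 is looser throughout on the mean reading and can never matter, or that it is far stricter throughout on the lowest-month reading. The table supports neither. On the mean reading the rows agree at 0–29, 35–48 and 60 or more, and row 2 alone gives a colour at 34. On the lowest-month reading, nine patients every month is green on row 2 and amber on row 1.

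A reader might also take the 32% as a property of the plan. It is not. It depends on the lowest-month reading and on the Poisson assumption, and the shared target of 84 = 14 × 6 gives some support to the mean reading, on which the figure does not arise.

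Finally, amber allows adaptations to be proposed and red calls for a discussion. Nothing stops automatically, recruitment continues while the report is prepared, and the DMC advises the steering committee. That also stands, and it limits the importance of the point.

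**Conclusion.** The point holds as an internal inconsistency in the stated thresholds, of minor consequence. Three parts are certain from Table 2: 34 has no colour on row 1, 70% has two on row 3, and the recruitment cut-points do not convert into each other (54 against 60, 30 against 35) although the targets do. On the mean reading, row 2 leaves 49–53 without a band and adds almost nothing to row 1. On the lowest-month reading it is a distinct and noisy criterion, missed about 32% of the time at full target recruitment if months are independent Poisson.

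A reader might conclude that the two rows flatly contradict each other, or that the trial could be wrongly halted. The documents do not support that: the worst-row rule resolves the between-row disagreements, and a non-green result leads only to proposals or discussion. The primary analysis, the error rates and the sample size ("it is calculated that 100 patients per group, 200 in total, are required") are untouched.

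**What to change.** 1. Row 1: make red below 35, so that it meets the amber band.
2. Row 3: make amber 50% to below 70%.
3. Row 2: state that the rate is the 6-month mean, and drop the row as redundant with row 1. If the slowest month is intended, say so and report it descriptively, not as a separate trigger.

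These are wording changes that cost nothing in patients or data, but timing matters. Recruitment began in June 2025 and the article is dated 30 December 2025, so the 6-month pilot was probably complete, or nearly so, at publication. If the review has already been held, the trial should record through the Trial Steering Committee which reading of row 2 was applied and how any boundary value was classified. Any amendment should be documented in the same way, so that the thresholds do not appear to have been moved after the recruitment they judge.

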### Indemnity arrangements

If there is negligent harm during the clinical trial when the NHS body owes a duty of care to the person harmed, NHS Indemnity covers NHS staff conducting the trial. NHS Indemnity does not offer no-fault compensation and is unable to agree in advance to pay compensation for non-negligent harm. The sponsor will provide post-trial care for complications or adverse events arising in trial patients following their operation.

### Data protection

Participant information will be kept confidential and managed in compliance with the Data Protection Act 2018, General Data Protection Regulations (GDPR), NHS Caldicott Principles, and the conditions of REC Approval. The Principal Investigator is responsible for maintaining strict confidentiality of locally stored trial documents, such as signed consent forms and quality of life questionnaires. The sponsor may require access to patient records for quality assurance and source data verification. In the event of specific issues or inquiries from regulatory authorities, access to the complete trial records may be necessary, provided patient confidentiality is safeguarded.

### Data storage

Following study end, patient-identifiable information will be kept for 3 years, after which all identifiable information, except for a list of local hospital numbers and corresponding unique study identifiers, will be confidentially destroyed. This list will be preserved as a method of record linkage to the research dataset to enable secondary research use in the future. Hard copies of study documentation such as quality-of-life questionnaires will also be destroyed by confidential means after transcribing onto REDCap. The full REDCap dataset will be moved to an encrypted version and archived indefinitely on UCL’s data safe haven.

### Publication policy

Research results will be published in peer-reviewed journals with the highest possible impact factor and those deemed appropriate by the PI. All proposed publications will be discussed with and reviewed by the TSC before publishing. Safety data will be reported descriptively and presented in the supplementary material.

